## **STUDY PROTOCOL**

This study is part of the EU-sponsored project DiOGenes (1), which is funded by the EU Sixth Framework Programme under Priority 5: Food Quality and Safety (Web-site: [www.diogenes-eu.org](http://www.diogenes-eu.org)) ( FP6-513946). DiOGenes comprises 5 strategic Research, Technological and Development (RTD) lines, each with its specific objectives. This protocol describes the dietary intervention study which is to be carried out by RTD line 1 (Obesity and macronutrient composition of the diet).

# 1. SYNOPSIS

## Study

DiOGenes is a randomised controlled dietary intervention study in obese/overweight families (adults and children) in 8 different European countries, testing the efficacy and safety of diets differing in Glycaemic Index (GI) and protein content.

## Aims

The main objective of the DiOGenes study is to identify the efficacy of particular diets for protection against weight gain and weight regain, in a susceptible population of obese and overweight individuals and their children. The overall study comprises a 6 to 12 months dietary intervention study in 350 families in 8 European countries (Denmark, the Netherlands, UK, Germany, Spain, Greece, Bulgaria and the Czech Republic), investigating the effect of different dietary components (high/normal protein and high/low GI) on maintenance of weight loss and prevention of weight (re)gain. In Denmark/Netherlands the study will be carried out over 12 months, in about 50 families. The responsiveness of the families to different dietary compositions and effects on body weight control and obesity related risk factors will be assessed during the dietary intervention study, with specific focus on changes in body weight and composition, appetite measures, adipose tissue gene expression and risk factors for cardiovascular disease (CVD) and type-2 diabetes. The role of genetic, environmental, social and cultural factors as well as their interactions with the studied diets on body weight control or development of obesity will also be investigated.

Primary outcome measures for adults are body weight loss maintained (kg), change in body composition, proportion of subjects maintaining > 0, 5 and 10% weight loss, and drop-out rate. Other non-clinical primary measures are to identify biological and psychological traits that determine the family's and individual's responses to the dietary interventions. Secondary end-points are reduction in abdominal obesity, changes in risk factors of type-2 diabetes and CVD and appetite/satiety hormones, and changes in physical activity. Clinical measurements will include in addition the identification and quantification of adipose tissue mRNA and peptide biomarkers. Primary outcome measures for children are changes in the proportion of overweight and obese children at 6 mo, and changes in BMI, and % whole body fat. Secondary end-points for overweight children are reduction in abdominal obesity, changes in waist-hip circumference ratio and blood parameters and changes in physical activity. A sub-study (described below) will assess the effect and safety of the high protein diet in children and adolescents. Dietary effects on bone and kidney health will be assessed and primary safety end-points will include changes in urinary and blood proteins, such as albumin and creatinine.

## Subjects

Families where both parents are < 65 years old, and where at least one parent is obese (BMI>30 kg/m^2) and the other is overweight (BMI>28 kg/m^2) will be offered inclusion in the study with the aim of losing weight and maintaining the weight loss. Families will have 1-3 children, and at least one child aged between 5 and 18 years will be overweight (defined according to Cole *et al.* (2), i.e. with an iso-BMI>25). A total of 150 adult subjects plus children (75 families) will be screened and approximately 135 adults are expected to be included in the initial weight loss phase of the study, with the aim of having a total of 110 subjects for the subsequent randomization to the 5 dietary

arms. This number will provide an anticipated completion of more than 80 subjects at the 12-month visit.

Subjects will be recruited through the department's waiting list, local press or via referrals from local general practices or from other medical departments. Radio/television or newspaper advertising may also be employed if necessary. Eligible subjects will only be included after they have been informed about the study and signed informed consent forms (including children, see Section 11).

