## 4.2 METHOD OF ASSIGNING FAMILIES TO DIETARY GROUPS

The eligible families will be allocated to a dietary intervention group using a simple block randomization procedure with centre, number of obese parents in the family and BMI (greater or less than 34, screening value) as stratification criteria by a third party with no knowledge of the

subjects that may affect the outcome of the study. Approx. 11 families are randomized to each of the 5 dietary intervention groups. The outcome in the dietary intervention groups will be compared to each other and to the control group.

Approx. 6 subjects in each dietary group (3 men and 3 women) will be randomized to **Subgroup a** (7-day food record, BMR and DLW measurements, physical activity using pedometers, meal test). Approx. 7-10 subjects in each dietary group will be randomized to **Subgroup b** (extra fat biopsy day 3 into LCD diet).

Participation by (adult) subjects in the sub-groups is entirely voluntary and separate information sheets and consent forms will be signed.

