## 5. SUBJECTS

An estimated 75 families will undergo screening. Thus it is aimed to enrol a total of about 50 families in the dietary intervention study, allowing for drop-out.

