### 5.1 INCLUSION CRITERIA

The inclusion criteria for the families are as follows:

- Families where both parents are < 65 years old, and where minimum one adult parent is obese (BMI>30) and the other parent is BMI>28.
- Families with 1-3 children, where at least one child aged between 5 and 18 years is overweight (defined according to Cole *et al.* (2), i.e. with an iso-BMI>25).
- Single-parent families with one obese (BMI>30) parent and minimum 1 overweight child aged between 5 and 18 years. Any other adult family members (including offspring) are excluded from the study. Children above the age of 16 may be excluded if they so wish.
- Healthy and no regular medication (exception oral contraceptives)
- All ethnic groups are allowed inclusion
- Smoking is allowed, provided subjects do not intend to change their smoking behaviour.
- All subjects should have an overall physical and psychological condition that the investigator believes is in accordance with the overall aim of the study.

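### The screened and randomised adult targets assume two adults in every family although single parents are eligible, and about 50 families cannot supply 110 randomised adults

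*Protocol*

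**What the plan says.** The Synopsis (Subjects) gives a chain of adult numbers. At screening and at entry to the low-calorie diet (LCD) phase: "A total of 150 adult subjects plus children (75 families) will be screened and approximately 135 adults are expected to be included" in that phase. At randomisation: "with the aim of having a total of 110 subjects for the subsequent randomization to the 5 dietary" arms. At the end: "This number will provide an anticipated completion of more than 80 subjects at the 12-month visit".

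Family numbers stand elsewhere. Section 4.2: "Approx. 11 families are randomized to each of the 5 dietary intervention groups". Section 5: "Thus it is aimed to enrol a total of about 50 families in the dietary intervention study", after an estimated 75 are screened. Section 3 likewise gives approximately 50 families in Denmark out of 75 screened, while the Synopsis (Aims) attaches about 50 families to Denmark/Netherlands.

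On who counts as a family, section 5.1 lists two-parent families and then adds: "Single-parent families with one obese (BMI>30) parent and minimum 1 overweight child aged between 5 and 18 years". The Synopsis (Inclusion criteria) says the same. Section 5.1 also excludes any other adult family member, grown-up offspring included. No section gives an expected share of single-parent families.

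**The concern.** The adult targets can be met only if every family brings two adults, but the eligibility rules allow one and forbid more than two. Any single-parent family therefore lowers the count and nothing can raise it again. Separately, sections 3 and 5 give a smaller number of families than section 4.2, and the smaller number does not reach the Synopsis target even if every family is a couple.

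At stake is whether the stated numbers can be delivered. A centre that enrols the families named in sections 3 and 5, and recruits single parents as section 5.1 permits, will have followed the protocol and still missed the randomised number in its Synopsis. The completion figure rests on that number.

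**Working it through.** **Inputs.** Synopsis (Subjects): 75 families and 150 adults screened, 135 adults in the LCD phase, 110 randomised, more than 80 completing. Section 4.2: about 11 families in each of 5 groups. Sections 3 and 5: about 50 families. Section 5.1: one or two adults per family. The single-parent share *s* is not given; 10% to 30% is assumed here only to show the range.

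**Reproducing the plan's figures.**
- Screened: 150 / 75 = 2.00 adults per family.
- Randomised: 5 × 11 = 55 families, and 55 × 2 = 110 adults. Both match exactly with *s* = 0.
- LCD phase: 135 / 2 = 67.5 families, so strict two-per-family counting cannot be shown at this step. Loss of individual adults could explain it.
- Implied retention: 80 / 110 = 72.7%. This is a floor, since the plan says more than 80.

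**Fifty families.** 50 × 2 = 100, which is 10 below 110. Reaching 110 would need 110 / 50 = 2.2 adults per family, above the ceiling of two.

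**Allowing for single parents.** Before any individual loss, adults = families × (2 − *s*). Retention needed for 81 completers = 81 / adults.

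| *s* | Adults screened from 75 families | Adults from 50 families | Retention needed for 81 of these | Adults from 55 families | Families needed for 110 adults |
|---|---|---|---|---|---|
| 0 | 150 | 100 | 81.0% | 110 | 55 |
| 10% | 142.5 | 95 | 85.3% | 104.5 | 58 |
| 20% | 135 | 90 | 90.0% | 99 | 62 |
| 30% | 127.5 | 85 | 95.3% | 93.5 | 65 |

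At *s* = 40%, 50 families give 80 adults, so 81 completers are out of reach. At *s* = 20%, 75 screened families give 135 adults, the number planned to enter the LCD phase, which leaves no room for screening failures.

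**Completers at the floor.** 100 × 80/110 = 72.7 from 50 couples. This is what the lowest retention compatible with the plan would give; it is not a forecast.

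**The case against.** The family counts are all approximate, and 50 and 55 differ by only five. Sections 3 and 5 mention drop-out beside the count, so 50 might be meant net of some attrition; 55 randomised and 50 remaining would then not conflict. The 110 is an aim, not a quota. Two-parent families come first in the eligibility text, so two adults per family is a natural planning shorthand.

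Part of this stands. The approximate wording and the drop-out remark soften the 50 against 55 discrepancy. However, section 5 speaks of enrolling families into the intervention study, and section 3 sets the drop-out allowance beside the 75 screened, so entry to the intervention is the more natural reading. Neither point touches the ceiling of two adults, because single parents can only lower the count.

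A reader might go further and infer that 50 families cannot produce more than 80 completers. The documents do not support that: 50 couples with 81% retention give 81. Nor do they support a specific lower forecast of completers, which would combine an assumed single-parent share with a retention floor treated as an estimate. Finally, this is not a finding about power. Section 8.2.7 derives 125 participants per group separately, without using these head counts.

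**Conclusion.** The point holds as an internal inconsistency in the recruitment figures. The 150 screened adults, and the 110 randomised adults when read with section 4.2, leave no room for a single-parent family, although such families are eligible. About 50 families supply at most about 100 adults, roughly 10 below the stated 110, and this follows from document figures alone. The lower values of 95, 90 and 85 depend on the assumed shares.

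The completion target is attainable from 50 families only with retention of at least 81% if all are couples, rising to about 85%, 90% or 95% at the assumed shares. The protocol states no retention assumption; its own figures imply only a floor of about 73%. If 50 was meant as the families remaining after drop-out, the shortfall against 110 disappears, but the two-adult assumption remains and the stage needs to be stated.

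**What to change.** - Choose one randomised-family count, about 50 or about 55. Use it consistently in the Synopsis (Aims and Subjects) and sections 3, 4.2 and 5, and say which stage it describes.
- State an expected single-parent share *s* and restate screened adults as 75 × (2 − *s*).
- Restate randomised adults as randomised families × (2 − *s*), less adults lost individually. The bare product cannot be carried past screening, because sections 5.3 and 7.8.2 let the rest of a family continue when one member leaves.
- Derive completers from an explicit retention assumption.
- If 50 families is kept, replace 110 with at most about 100 (95, 90 or 85 at *s* of 10%, 20% or 30%), and make the figure of more than 80 completers conditional on the stated retention.

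Restating the figures changes text only, though the targets become less favourable. It needs no extra recruitment and no change to design or eligibility. Keeping 110 instead would take 55 families if all are couples, or 58, 62 or 65 at the assumed shares, and that does mean more recruitment than 50 families.

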### Inclusion criteria

Families with 1 obese ( $\text{BMI} > 30 \text{ kg/m}^2$ ) and 1 overweight ( $\text{BMI} > 28 \text{ kg/m}^2$ ) parent, with 1-3 children, one of whom must be aged 5-18 and overweight (iso- $\text{BMI} > 25$ ). Single-parent families with one obese ( $\text{BMI} > 30 \text{ kg/m}^2$ ) parent and minimum 1 overweight child aged 5-18 will also be included.

### Exclusion criteria

**Adults:** Body weight changes more than  $\pm 3 \text{ kg}$  within the last 2 months, pregnant or lactating women, subjects with heart or coronary diseases, kidney or liver diseases, psychiatric illnesses, systemic infections or endocrine diseases, a history of malabsorption, subjects with any clinical condition that renders them unfit to participate, hypertensive and/or hypercholesterolaemic subjects with pharmacological changes within the last 2 months, systolic blood pressure (SBP)  $> 160$  and/or diastolic blood pressure (DBP)  $> 100 \text{ mmHg}$ , subjects on special diets.

**Children:** Subjects with systemic infections or chronic disease, or on special diets.

### Dietary periods

- 1) Adult subjects only: 8 week Low Calorie Diet (LCD) period (liquid formula diet, 800-1000 kcal/day).
- 2) 6 months dietary intervention period 1 (SUPERMARKET period) followed by
- 3) 6 months dietary intervention period 2 (DIETARY INSTRUCTION period).
- 4) 12 months free-living period with no dietary intervention.

[figure not shown]

### Diets and randomization

Families will be randomised into 5 dietary groups during dietary intervention periods 1 and 2:

Group 1: Normal protein/low GI  
Group 3: High protein/low GI  
Group 5: Control diet

Group 2: Normal protein/high GI  
Group 4: High protein/high GI

The eligible families will be stratified based on centre, number of obese parents and BMI. Within the strata the subjects will be randomized to treatment (and sub-study groups) using a simple block randomization method by a third party having no knowledge of the subjects that may affect the outcome of the study.

### **Dietary intervention study**

All adult subjects will for the first 8 weeks of the study be submitted to an 800-1000 kcal/day LCD diet combined with instructions on behaviour modification. Only families where at least 1 parent has achieved a >8% weight loss will be included in the intervention study. The study consists of a 6-month dietary intervention period (period 1, SUPERMARKET period) where families obtain free food from an on-site supermarket and receive continual dietetic guidance, followed by a further 6-month period (period 2, DIETARY INSTRUCTION period) where families receive dietary and behavioural instruction. Families will regularly visit RVAU/UM throughout the intervention period for weighing and dietary instruction. There are 4 Clinical Investigation Days (CIDs) planned during the study, when anthropometric and other measures will be taken. CID 1 will take place in the 3 weeks prior to the LCD diet. CID 2, 3 and 4 will take place in weeks 0, 26 and 52, respectively.

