## **2. 6 months dietary intervention period 1 (SUPERMARKET period)**

Families in which at least one parent has achieved an 8% loss of initial body weight will be randomised to one of 5 dietary arms (see Table 1), including a control group. Subjects enrolled in the 4 intervention groups will be expected to get most of their foods free of charge in the supermarket for the first 6 months of the intervention. The on-site supermarket has fresh, shelved and frozen products, separated according to the dietary design. All food items will be bar-coded and a dietician will scan the barcodes of all the chosen items to monitor macronutrient composition of the diet and will assist in altering the selection to meet the prescribed macronutrient composition. Each food item scanned will be registered in a database in the shop. The calculated energy content of the chosen groceries will not be made known to the subjects. The control group will be instructed to continue their habitual dietary intake whilst shopping in ordinary food shops (thus their food will not be free).

Families in all intervention groups will receive careful, intensive and regular dietary and behavioural guidance during both intervention periods 1 and 2, although the control group will not receive advice regarding dietary composition. The dietary instruction will include family sessions, where instruction will be given to the whole family, including children. The dietician will advise on weight control and reinforce the diet composition through recipes, cooking advice, and behaviour modification in group (several families) and individual meetings (one family). Subjects will be given oral and written instructions relating to the five intervention groups based on an exchange system. The aim is to reach the required macronutrient composition on a daily basis. Hence, individual meals (breakfast, lunch, dinner) may not necessarily have the designated macronutrient composition. During intervention periods 1 and 2, weight maintenance is attempted, though further weight reduction will be allowed, i.e. in all 5 groups, the diet intervention is carried out with less emphasis on the calorie content of the diet (which is *ad libitum*) or the calorie density of the diet, but with major emphasis on adherence to the diet prescribed. Hence, during both periods 1 and 2 it is the diets' ability to satisfy and to regulate appetite and body weight that will be tested.

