### 5.2 EXCLUSION CRITERIA

The exclusion criteria for the adults are as follows:

---

 Children below the age of 5 are excluded and should continue to eat according to local dietary guidelines

*At enrolment:*

- Use of prescription medication marked with N
- Blood pressure above 160/100 mmHg (Subjects with SBP=159 and DBP=99 are allowed inclusion). Well regulated BP (<140/90 mmHg) using drugs is allowed if no change in BP and drug dose within last 3 months.
- Fasting blood glucose >6.1 mM at screening. Re-test is allowed.
- Known untreated hypercholesterolemia (>7 mM). Subjects using drugs for hypercholesterolemia are excluded.
- Known untreated hypertriglyceridemia (>3 mM). Subjects using drugs for hypertriglyceridemia are excluded.
- Drug-treated thyroid diseases (well substituted hypothyroidism is allowed inclusion)
- food allergies
- special diets (e.g. vegetarian, Atkins) within 2 months prior to study start
- Food intolerance expected to interfere with the study
- Regularly drinking > 21 alcoholic units/week (men), or > 14 alcoholic units/week (women)
- Elite athletes and subjects planning to engage in elite sports (i.e. planning major changes in physical activity during the study).
- Blood donation within the past 3 months before entering the study.
- Weight change of > 3 kg within 2 months prior to Clinical Investigation Day
- Mental disorders
- Eating disorders
- Pregnant or lactating women, or women who are planning to become pregnant within the next 18 months.
- Surgically treated obesity
- Participation in other clinical studies within the last 3 months
- Alcohol or drug abuse (based on clinical judgment)
- Subjects who are unable to give informed consent.
- Subjects with systemic infections
- Subjects with endocrine disease
- Subjects with malabsorption
- Subjects who are unable to engage in a 8 week LCD period

*At randomisation:*

- Families in which both adults fail to lose min. 8% of initial body weight during LCD period

The exclusion criteria for the overweight children are as follows:

- special diets (e.g. vegetarian, Atkins) within 2 months prior to study start
- food intolerance expected to interfere with the study
- Regularly drinking > 21 alcoholic units/week (male), or > 14 alcoholic units/week (female)
- Blood donation within the past 3 months before entering the study.
- Subjects with systemic infections / chronic disease
- Use of chronic medication, except for conditions like hayfever

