### 8.2.2 MAIN OUTCOME MEASURES

The main outcome measures in this study for adults are body weight loss maintained (kg), changes in body composition (DEXA/bioimpedance), proportion of subjects maintaining > 0, 5 and 10% of initial weight loss, and drop-out rate. Main outcome measures for children are changes in the proportion of overweight and obese children at 6 and 12 mo, and changes in age-associated BMI, % whole body fat and drop-out rate.

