### 8.2.4 STATISTICAL METHODS FOR THE PRIMARY OBJECTIVES

Analysis of Covariance (ANACOVA) will be used to compare the main outcome measures in the intervention groups at week 26 and week 52 using the data from CID2 (after weight-loss, adults) or CID1 (children) as covariate.

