### **8.2.7 SAMPLE SIZE ESTIMATION**

The primary aim of the study is to investigate the long-term efficacy in terms of change in body weight from baseline to study end. The sample size for the proposed study was chosen to provide sufficient power to detect differences in 26-week weight regain (for primary participants) due to the effects of the different diets. The sample estimation is based on the difference between the intervention and control groups regarding weight change (kg) from baseline to week 26. In the null hypothesis we assume that the interventions groups 1 - 4 are of equal weight at week 26 compared to baseline, while the alternative hypothesis assumes that there exists a difference in weight between the treatment groups. By this covariate method we are able to test the change from baseline to week 26 while controlling for between-group differences in the baseline value.

It is anticipated that weight differences will be smallest between the low vs. high GI diets compared to the low protein vs. high protein diets. Hence the sample size has been calculated on the basis of a previous intervention study on GI (18), which found a non-significant difference in body weight change of 0.6 kg between groups using the unpaired t-test. We assume a 0.4 kg higher weight loss based on 6-month treatment, compared to the 10-week previous intervention study (18). Thus we consider that a weight loss difference of 1 kg is a clinically relevant weight loss and a priori we assume a SD of 2.01 kg.

When assuming a difference between control and intervention group of 1.0 kg (SD 2.5 kg), at least 80% statistical power and a significance level of 5%, N=125 participants per group are required (unpaired t-test). In this model, any effect size above 0.72 kg gives a power of more than 80%.

As most other studied variables in the study are secondary objectives and because the outcome of most of these variables are not easily comparable to previous studies due to the novel design of the study, there are no calculations on sample size for variables other than the primary efficacy parameter, which is weight change to week 26.

Thus, in terms of final outcome, it is accepted that post-hoc analysis will identify that not all measures of other primary or secondary outcomes will necessarily have had the appropriate sample size.

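### The 8% LCD criterion selects families rather than adults, and the adult ANCOVA controls only for the CID 2 value, so variation in LCD loss stays in the error term

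*Protocol*

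**What the plan says.** The entry rule after the LCD is set by family throughout. The synopsis states "Only families where at least 1 parent has achieved a >8% weight loss will be included in the intervention study". Section 3, on the supermarket period, states "Families in which at least one parent has achieved an 8% loss of initial body weight will be randomised". At randomisation, section 5.2 excludes only "Families in which both adults fail to lose min. 8% of initial body weight during LCD period". Nothing removes a parent who fell short of 8% when the partner reached it.

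Both parents are counted as adult subjects. The synopsis plans recruitment "with the aim of having a total of 110 subjects for the subsequent randomization to the 5 dietary" arms, and section 4.2 says "Approx. 11 families are randomized to each of the 5 dietary intervention groups". Section 8.2 allows subjects to be left out of the efficacy analysis only for a protocol violation, and a small LCD loss is not one.

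Section 8.2.2 says "The main outcome measures in this study for adults are body weight loss maintained (kg"), together with body composition and responder proportions. Section 8.2.4 compares the groups at weeks 26 and 52 "using the data from CID2 (after weight-loss, adults) or CID1 (children) as covariate", and section 8.2.5 words the hypothesis the same way. LCD loss is not a covariate, nor is it one of the stratification factors in section 4.2 (centre, number of obese parents, screening BMI). Section 8.2.7 speaks of "26-week weight regain (for primary participants") and never defines that group.

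**The concern.** The outcome is how much of a loss is kept, but the model sees only where each adult stood when the loss ended. Take two parents who both weigh 90 kg at CID 2, one down from 92 kg (2/92 = 2.2%) and the other from 105 kg (15/105 = 14.3%). Their family qualifies through the second parent. In the same arm, a model with CID 2 weight alone predicts the same week-26 weight for both, although one has 2 kg to regain and the other 15 kg.

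If the amount lost predicts the amount regained, that difference is explainable variation left in the error term. The confidence interval for every diet contrast is then wider than the data already collected would allow.

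**Working it through.** The Protocol gives no figure for the spread of LCD loss or for its relation to regain, so there is no stated figure to reproduce on this point. The sample-size figures in section 8.2.7 are not used except where named.

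**1. How many adults could be below 8%.** Families: 11 × 5 = 55 (section 4.2). Adults: 110 (synopsis). 110 / 55 = 2.0 per family, so the rule would admit up to 55 of 110 adults below 8%. That is a ceiling, not an estimate. Assuming a mean loss of 8–11%, an SD of 2.5–3.5 percentage points and a spouse correlation of 0–0.5, about 8% to 33% of adults in qualifying two-parent families fall below 8%, and about 0.4% to 13% below 5%.

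**2. Residual variance that CID 1 would explain.** Assumed inputs: CID 1 weight SD 15 kg; LCD loss L with SD 4 kg, independent of CID 1 weight; regain = b × L + noise, with total regain SD 4.5 kg (variance 20.25); b = 0.2 to 0.5.

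- CID 2 weight = CID 1 weight − L, so its variance is 225 + 16 = 241, and its covariance with L is −16.
- Variance of L given CID 2 weight = 16 − 16²/241 = 14.94. CID 2 weight therefore says almost nothing about L.
- Noise variance = 20.25 − 16b².
- Outcome week-26 weight: share removed = 14.94b² / (14.94b² + 20.25 − 16b²).
- Outcome loss maintained from CID 1, which equals (1 − b)L − noise: share removed = 14.94(1 − b)² / (14.94(1 − b)² + 20.25 − 16b²).

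| b | Week-26 weight | Loss maintained from CID 1 |
|---|---|---|
| 0 | 0% | 14.94/35.19 = 42% |
| 0.2 | 0.60/20.21 = 3.0% | 9.56/29.17 = 33% |
| 0.3 | 1.34/20.15 = 6.7% | 7.32/26.13 = 28% |
| 0.4 | 2.39/20.08 = 11.9% | 5.38/23.07 = 23% |
| 0.5 | 3.74/19.98 = 18.7% | 3.74/19.98 = 18.7% |

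The two outcomes meet at b = 0.5; below that, loss maintained from CID 1 suffers more. For week-26 weight, the interval narrows by 1 − √(1 − 0.030) = 1.5% up to 1 − √(1 − 0.187) = 9.8%.

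**3. Check by simulation.** 126 adults per arm in two-parent families, LCD loss mean 10% (SD 3%), regain SD 2.5 kg and true effect 1.0 kg (the last two from section 8.2.7). The mean estimate was 0.98 to 1.00 kg in every setting, with or without LCD loss in the model, so there is no bias. The SD of the estimate, CID 2 only versus CID 2 plus LCD loss:

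- Week-26 weight: 0.31 to 0.31 kg (b = 0), 0.31 to 0.30 (b = 0.2), 0.32 to 0.28 (b = 0.4).
- Loss maintained: 0.49 to 0.31 kg, 0.44 to 0.30 and 0.35 to 0.27 at the same slopes.

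**4. CID 1 weight or LCD loss.** Since L = CID 1 − CID 2, a model with CID 2 and CID 1 weight is the same as one with CID 2 weight and L. With both in the model, week-26 weight and loss maintained from CID 1 give the same diet contrast apart from sign, because they differ only by a covariate.

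**The case against.** **The covariate may already be the LCD loss.** Section 8.2.5 controls for the value at CID 2. If the outcome is loss maintained, its own value at CID 2 is CID 1 minus CID 2, which is the LCD loss. This is possible but strained, because section 8.2.5 gives weight as its example of the outcome. The large precision cost does need a particular pairing, loss from CID 1 as outcome with CID 2 weight as covariate, which the text allows but does not require.

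**A reader might infer bias, or a chance imbalance large against the 1.0 kg target.** Neither is supported. Allocation follows the LCD, so losses are balanced in expectation, and chance imbalance is already in the standard error. Judging an imbalance of, say, 1.5 kg at 22 adults per arm against 1.0 kg also mixes two scales, since section 8.2.7 sets that target for 125 per group. With a loss SD of 4 kg and clustering ignored, the standard error of an arm difference in loss is 4√(2/22) = 1.21 kg locally, but 4√(2/125) = 0.51 kg at the planned size. So 1.5 kg is 1.2 standard errors in one case and 3.0 in the other.

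**A reader might infer that adults with little loss dilute the diet effect.** That needs a diet effect that grows with the kilograms lost. The documents do not state one, and the model above has none. The synopsis also aims at preventing weight gain as well as regain, and such adults inform that aim.

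**It is a matter for the SAP.** The Protocol itself fixes the covariate and the hypothesis, so the comment is on stated text. Entry by family is a legitimate choice in a family trial and is not criticised here.

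**Conclusion.** The point stands as one of precision. The family-level rule admits adults with widely differing LCD losses, and the stated adult ANCOVA controls only for the CID 2 value. The contrast is valid as planned. For week-26 weight, about 3–19% of residual variance could be removed if 20–50% of the loss is regained, and nothing if loss does not predict regain. If the outcome is loss maintained from CID 1, the share is about 42% when loss does not predict regain, 33% at 20% regained, and falls to the same 19% at 50%. All these figures rest on the assumed SDs and slopes, which the Protocol does not supply. This is a worthwhile, nearly free improvement and not a flaw that invalidates the analysis.

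**What to change.** In sections 8.2.4 and 8.2.5, for the adult weight and body-composition outcomes, name the CID 1 value as a second covariate beside the CID 2 value. Keep all randomised adults in the primary analysis regardless of their LCD loss; how non-completers are handled is a separate matter.

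Use the CID 1 measurement itself. It clearly precedes allocation, is already taken for every adult (section 7.1.1.2), and is weighed under the standard CID conditions of section 7.2.1. Week-0 weight would be ambiguous, because adults are weighed twice that week: at the randomisation meeting, where only coat and shoes must come off, and at CID 2.

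Optionally, report the week-26 and week-52 contrasts in adults who themselves lost more than 8% as a supportive analysis. Do not define the primary participants of section 8.2.7 as that subgroup, since the sample-size text would then describe a different population from the primary analysis.

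Cost: one degree of freedom, at most one supportive table, and no new data.
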